## 2. Failure to return for evaluation as a result of death or deteriorating condition

In this instance, the earliest known date of death or deterioration will be used as the date of progression. Where unknown, the clinical assessment date at which the patient did not attend will be used (only for patients known to have not returned for evaluation due to death or deteriorating condition).

*As determined by retrospective radiographic central review:*

3. **Any new lesion** (short axis must be  $\geq 10$  mm on at least 2 axial slices that are 5mm apart with 0mm skip and the new lesion should be outside the original tumour volume)
4. **Increase in  $\geq 25\%$  of sum of the products of perpendicular diameters of enhancing lesions compared with baseline scan, on stable or increasing doses of steroids (dexamethasone) compared to baseline (T1 post-contrast scan)**
5. **Clear progression of non-measurable disease** (clinically significant increase in size with a short axis  $\geq 10$ mm on at least 2 axial slices that are 5mm apart with 0mm skip)
6. **Significant increase in T2/FLAIR non-enhancing lesion – on stable or increasing steroids (dexamethasone) compared with baseline or best response not caused by co-morbid events.** Precise quantification of the increase in T2/FLAIR signal can be difficult and must be differentiated from other causes of increased T2 or FLAIR signal, such as radiation effects, decreased corticosteroid dosing, demyelination, ischemic injury, infection, seizures, postoperative changes, or other treatment effects before making a determination of progressive disease. Changes in T2/FLAIR signal that suggest infiltrating tumour include mass effect (as determined by sulcal effacement, ventricular compression, and thickening of the corpus callosum), infiltration of the cortical ribbon, and location outside of the radiation field. The initiation of these changes can be subtle, and convincing non-contrast-enhancing growth may require one or two confirmatory scans. If non-enhancing progression is determined after retrospective review of images, the scan at which these changes were first detected should serve as the progression scan.

Examples of progression on T2/FLAIR:

- a. Substantial change in size of tumour with clear margins on T2/FLAIR
- b. New lesion(s) ( $\geq 10$ mm) which is completely distinct from original enhancing volume on T2 ( $\geq 50$ mm distance)

Change in signal intensity in T2/FLAIR within the original enhancing volume would not be sufficient for evidence of tumour progression.

The date of progression will be determined as being the date of the first MRI scan fitting the criteria for progression, or the date the clinical deterioration or death was first reported, whichever is earliest.

Locally reported progression should be determined by the above criteria. However, due to the possibility of pseudoprogression in these patients, a confirmatory second scan taken 6 weeks after the first should be used when making treatment decisions based on radiological progression. Please note it is not necessary to stop the trial drug in patients who have progressed only radiologically (even if confirmed at subsequent visits) if the clinician feels that the patient is benefiting from treatment.

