#### 2.4.1.1 Phase III study of cediranib versus lomustine versus cediranib plus lomustine in glioblastoma

The results of a recent phase III trial in recurrent glioblastoma using cediranib and lomustine (the REGAL trial) were presented at the European Society for Medical Oncology (ESMO) congress, 2010 (Bachelor et al, 2010). Patients were randomised at 2:2:1 to cediranib alone (30mg od), cediranib (20mg od) plus lomustine (110mg/m^2 every 6 weeks), or lomustine alone (110mg/m^2 every 6 weeks) and placebo.

325 patients were randomised: Ced (n=131), Ced + Lom (n=129) or Lom (n=65). The study showed no statistical difference between either cediranib arm vs. lomustine alone on the primary endpoint of progression free survival (Ced vs Lom: HR=1.05, 95% CI 0.74–1.50, P=0.899; Ced + Lom vs. Lom:

HR=0.76, 95% CI 0.53–1.08; P=0.162 [median PFS (days): 92 (ced), 125 (ced+ lom), 82 (lom)], or for overall survival (Ced vs Lom: HR=1.43, 95% CI 0.96–2.13, P=0.100; Ced + Lom vs. Lom: HR=1.15, 95% CI 0.77–1.72; P=0.499 [median OS (months): 8.0 (ced), 9.4 (ced + lom), 9.8 (lom)]). Cediranib did show evidence of clinical activity at other endpoints, including a statistically significant increase in the time to deterioration of neurological status when cediranib was given with lomustine compared to lomustine alone (Ced vs Lom:HR=0.82, 95% CI 0.55–1.22, P=0.573; Ced + Lom vs. Lom: HR=0.63, 95% CI 0.42–0.95, P=0.009 [median TDNS (days): 126 (ced), 170 (ced + lom), 111 (lom)]). There was also a numerical increase in the cediranib-containing arms with regards to response rate – which was not determined by RANO criteria (Wen 2010), (15.3% (ced), 17.2% (ced + lom), 8.9% (lom)). The mean change in steroid use from baseline to progression was significantly reduced for both cediranib arms when compared to lomustine alone (-26.2% (ced), -23.4% (ced + lom), +5.3% (lom); ced vs lom = p0.006, ced+lom vs lom= p0.012). There was no increased risk of fatal outcome or intracranial bleeding in the cediranib arms.

Baseline characteristics were balanced across treatments, although the lomustine arm did have a slightly higher Karnofsky Performance Status and lower steroid use compared to the other arms.

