## 7.7 Other trial treatments/interventions: Imaging

Central to the collection of the outcomes of this trial is regular MRI brain scans at screening/baseline and 6-weekly thereafter.

The same MRI scanner should be used for all images for the patient throughout the trial where possible. There should not be any switching between magnets of different field strengths.

The screening/baseline scan should be performed within 7 days prior to the randomisation date. This scan will be used to determine whether or not the patient is eligible for the trial. Routine scans prior to baseline should be assessed when deciding whether or not a patient should be screened for the trial, but will not be collected for this trial.

The follow up scans must be performed +/- 10 days of the due date (every 6 weeks after the start of trial treatment), irrespective of the trial treatment administration. Follow up scans should be consistent with baseline scans with regards to modality, scanner and all associated scanning parameters.

If a patient discontinues from the trial treatment, the discontinuation MRI should be completed within 10 days of discontinuation (if possible).

Patients must be on a stable dose of steroids (dexamethasone) for at least 5 days prior to baseline scan and at least 10 days prior to all follow-up scans (where possible).

The following images will be taken on a 1.5 or greater Tesla MR scanner:

| IMAGE                                                                       | Orientation | Slice gap (mm) | Slice thickness (mm) |
|-----------------------------------------------------------------------------|-------------|----------------|----------------------|
| FLAIR (Fluid-attenuated inversion-recovery image)                           | Axial       | 0mm            | ≤ 5mm                |
| DWI (diffusion weighted image)
Spin echo –echo planar                    | Axial       | 0mm            | ≤ 5mm                |
| T2 (T2-weighted fast spin echo images)                                      | Axial       | 0mm            | ≤ 5mm                |
| T1 volumetric (three-dimensional gradient echo images)                      | Coronal     | 0mm            | ≤ 5mm                |
| Post-contrast T1 volumetric (three-dimensional gradient echo images) | Coronal     | 0mm            | ≤ 5mm                |
| Post-contrast FLAIR (Fluid-attenuated inversion-recovery image)      | Axial       | 0mm            | ≤ 5mm                |

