## 16.4 Statistical Analysis of the Secondary Endpoints

The secondary endpoints will be subject to an ITT analysis only.

- **Overall survival (OS)**

This is defined as time from date of randomization to date of Death due to any cause. This endpoint will be analysed in a similar way to the primary endpoint

- **Radiographic response rate (RR) at each assessment point**

The response rates will be summarised by treatment groups in terms of counts and percentages. The following definition of responses will be used.

- **Complete response:** Requires all of the following: disappearance of all contrast enhancing lesions on MRI compared to baseline sustained for 2 consecutive 6 weekly scans\*; no new lesions; stable or improved nonenhancing (T2/FLAIR) lesions; patients must be off dexamethasone (or on physiologic replacement doses only); and stable or improved clinically. Patients with non-measurable disease only cannot have a complete response; the best response possible is stable disease.
- **Partial response:** Requires all of the following:  $\geq 50\%$  decrease compared with baseline in the sum of products of perpendicular diameters of all measureable enhancing disease percentage change sustained for 2 consecutive 6 weekly scans\*; no progression of non measurable disease; no new lesions; stable or improved nonenhancing (T2/FLAIR) lesions on same or lower dose of dexamethasone compared with the baseline scan; the dexamethasone dose at the time of the scan evaluation should be no greater than the dose at the time of baseline scan; and stable or improved clinically. Note: Patients with non-measurable disease only cannot have a complete response; the best response possible is stable disease.
- **Progression:** (See [Section 2.6.1.1](#))

**Stable Disease:** Requires all of the following: a patient whose MRI scan does not meet the criteria for *Complete Response*, *Partial Response*, or *Progressive Disease*: stable nonenhancing (T2/FLAIR) lesions on same or lower dose of dexamethasone compared with baseline scan. In the event that the dexamethasone dose was increased for new symptoms and signs without confirmation of disease progression on neuroimaging, and subsequent follow-up imaging shows that this increase in dexamethasone dose was required because of disease progression, the last scan considered to show stable disease will be the scan obtained with the dexamethasone dose was equivalent to the baseline dose.

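### Criterion 4 ties enhancing growth to the baseline steroid dose alone, so a patient settled below that dose cannot progress on it; criterion 6 uses a different reference

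*Protocol*

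**What the plan says.** Section 2.6.1.1 of the protocol lists six criteria, any one of which is progression.

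- **Criterion 4** (enhancing lesions up 25% or more from the baseline scan) applies only "on stable or increasing doses of steroids (dexamethasone) compared to baseline (T1 post-contrast scan".
- **Criterion 6** (non-enhancing T2/FLAIR lesion) applies "on stable or increasing steroids (dexamethasone) compared with baseline or best response not caused by co-morbid events". Other causes of increased signal must first be excluded, among them "radiation effects, decreased corticosteroid dosing, demyelination, ischemic injury, infection, seizures, postoperative changes, or other treatment effects".
- **Criteria 3 and 5** carry no steroid condition. Criterion 3 is a new lesion, and "the new lesion should be outside the original tumour volume". Criterion 5 is non-measurable disease, with a "clinically significant increase in size with a short axis" of at least 10 mm.
- **Criteria 1 and 2** are clinical deterioration, and failure to return because of death or deterioration.

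Under Stable Disease, section 16.4 requires that the scan meet none of the other categories and show "stable nonenhancing (T2/FLAIR) lesions on same or lower dose of dexamethasone compared with baseline scan".

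The steroid endpoint (sections 2.6.1.2 and 16.4) measures an increase against baseline or a sustained nadir. Section 7.7 asks for a stable dose for "at least 10 days prior to all follow-up scans (where possible"). Section 2.5.2 makes steroid sparing a comparison between the arms.

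**The concern.** Every entrant must have measurable enhancing disease (section 5.1.1), and criterion 4 is the only rule for growth of that lesion. Its steroid condition looks back to the entry dose, however long ago that was. A patient on a settled lower dose is neither stable nor increasing relative to entry, so the growth does not count.

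Tapering is expected in this trial. Section 2.2.1 describes steroid sparing with anti-VEGF treatment. Of the earlier phase III trial, section 2.4.1.1 reports: "The mean change in steroid use from baseline to progression was significantly reduced for both cediranib arms". The means were -26.2% on cediranib alone, -23.4% on cediranib plus lomustine and +5.3% on lomustine.

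PFS is the primary endpoint, and the 24-week PFS rate and the progression/steroid-free days share its definition. The trial asks whether tapering differs between arms while using a PFS rule that depends on tapering, so any such difference would pass into PFS without a difference in tumour growth.

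**Working it through.** **1. Reading the rules together.** Take, as an example, a patient who enters on 6 mg/day (section 5.1.2 excludes more than 8 mg/day in the two weeks before randomisation), settles on 2 mg/day, and whose enhancing lesion then grows by 25% or more.

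| Rule | Applies at 2 mg/day? |
|---|---|
| Criterion 4 | No: the dose is below baseline |
| Criterion 6 | Arguably yes, if T2/FLAIR grows and the dose is unchanged since best response; the phrase is ambiguous and reduced dosing must be excluded as a cause |
| Criterion 3 | Only for a new lesion outside the original tumour volume |
| Criterion 5 | Only for non-measurable disease |
| Criteria 1 and 2 | On clinical deterioration or death |
| Stable Disease (16.4) | Yes if T2/FLAIR is stable; no if T2/FLAIR has grown |

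With stable T2/FLAIR the scan is stable disease. With T2/FLAIR growth that does not meet criterion 6, it is neither progression nor stable disease, and no category is left. The response rate is untouched, because a scan with 25% growth over baseline cannot be a complete or partial response.

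**2. The plan's own figure.** Inputs from section 16.1: medians of 4 and 6 months, one-sided error 10%, power 80%. With HR = 4/6 and 1:1 allocation, Schoenfeld's formula gives

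d = 4(z0.90 + z0.80)² / (ln HR)² = 4 × (1.2816 + 0.8416)² / (0.4055)² = 18.03 / 0.1644 = 109.7, that is 110 events.

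Power with 110 events is 80.1%. Both reproduce the plan.

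**3. Possible effect on the comparison.** The protocol gives neither the share of patients below their baseline dose when the tumour grows nor the resulting delay. The following are assumptions:

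- 56 patients per arm, uniform entry over 18 months, censoring at 36 months from the start of the trial;
- exponential PFS, with a control median of 4 months;
- 10% to 40% of an arm tapered;
- recorded progression in tapered patients delayed by a fixed 1.38 or 2.76 months (one or two 6-weekly scans);
- log-rank test, one-sided 10%, 6,000 runs per setting. The Monte Carlo standard error near 10% is √(0.1 × 0.9 / 6000) = 0.4 percentage points.

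The apparent HR is the ratio of events per person-time. With no true effect:

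| Tapered, control v combination | One-sided error, delay 1.38 / 2.76 | Apparent HR |
|---|---|---|
| 0% v 0% | 11.3% / 10.3% | 1.00 / 1.00 |
| 20% v 20% | 10.6% / 10.2% | 1.00 / 1.00 |
| 40% v 40% | 10.2% / 10.1% | 1.00 / 1.00 |
| 20% v 30% | 13.1% / 15.5% | 0.97 / 0.96 |
| 20% v 40% | 15.0% / 21.0% | 0.96 / 0.92 |
| 10% v 40% | 18.7% / 29.8% | 0.93 / 0.88 |

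The two 0% v 0% results come from the same setting, since no delay is applied; they show the noise. With a true HR of 0.667 and equal tapering (20% or 40%), power is 78% to 79% and the apparent HR is 0.68 to 0.70. More tapering in the control arm would push the bias the other way.

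**The case against.** **Comparing with baseline is coherent within criterion 4.** Lesion size is compared with the baseline scan, so comparing dose with baseline is a conservative way to keep growth caused by steroid reduction out of the count. The protocol itself lists reduced dosing among the non-tumour causes of T2/FLAIR change. This stands as a reason for caution, and it argues against replacing the reference with the 10-day stability window of section 7.7. That would be a new criterion, and it could count against the arm with more steroid sparing. It does not explain why criterion 6 and the steroid endpoint use a later reference while criterion 4 does not.

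**Other routes to progression remain.** A reader might infer that a tapered patient cannot progress on tumour growth at all, or is always scored as stable. The documents do not support that. Criteria 3 and 5 have no steroid condition, criterion 6 admits best response, clinical deterioration and death still count, and a return to the baseline dose reopens criterion 4. Patients on no steroids at entry cannot fall below baseline.

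**Both arms receive cediranib.** A reader might also infer that PFS is biased in favour of the combination. Treatment is double-blind, section 2.2.1 attributes steroid sparing to anti-VEGF treatment, and the two cediranib arms of the earlier trial had similar mean changes. The 26.2% is a mean change in dose, not a proportion of patients tapered. Nothing in the protocol supports a particular imbalance.

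**An exploratory analysis under unmodified RANO is planned (section 16.3).** What it would show on this point cannot be judged from the protocol, and it leaves the primary result unchanged.

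**Conclusion.** The point holds for criterion 4. Enhancing growth of any size on a settled below-baseline dose does not count, the steroid references in criteria 4 and 6 do not agree, and the classification in section 16.4 is either stable disease or missing, depending on T2/FLAIR. The usual consequence is a delay in recorded progression until another criterion is met or the dose returns to baseline.

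The size of the effect is not known from the protocol. With equal tapering, the simulation leaves type I error at about 10% and power at 78% to 79%. The inflation to about 13% to 30% appears only under the assumed imbalances and delays, so those figures show sensitivity and are not a forecast. The 110 events and 80% power stand. The point merits an amendment because it concerns the definition of the primary endpoint and because the trial itself sets out to test whether tapering differs between arms.

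**What to change.** 1. In section 2.6.1.1, give criterion 4 the same steroid reference as criterion 6: a dose stable or increasing relative to baseline or best response. Define that phrase once for both, so that a dose unchanged or higher since best response qualifies. Say also what serves as best response in a patient who never had better than stable disease.
2. In section 16.4, amend Stable Disease so that enhancing growth of 25% or more on such a dose is not scored as stable.
3. State how growth on a dose lowered since best response is classified and dated, for both enhancing and T2/FLAIR disease, so that no scan is left without a category.
4. Give the central reviewers the dexamethasone record.
5. Report PFS under the baseline-only reference as a sensitivity analysis.

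**Cost.** Wording in two sections and in the instructions for central review. Central review is retrospective at the end of the trial and dexamethasone is already recorded until progression, so no new scans or data are needed for the primary analysis. Sites apply the same criteria for locally reported progression and need the amended text.

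**Downsides.** Some growth partly due to a lower steroid dose may be counted as progression; the sensitivity analysis would show how much this matters. That analysis looks beyond the date at which the amended rule calls progression, and section 16.4 has daily dexamethasone recorded only until progression, so for some patients the later record may be short.

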#### **2.6.1.2 Secondary outcome variables**

- Overall survival (OS) – date from randomisation to death due to any cause
- Radiographic response rate (RR) at each assessment point
- PFS rate at 6 months (24 weeks). Progression is defined in the same way as described for the primary endpoint.
- Safety and tolerability
- Overall Survival rate at 12 months
- Time to sustained increase ( $\geq 21$  days) in steroid dosage by  $\geq 8\text{mg/day}$  compared to baseline or sustained nadir ( $\geq 21$  days)

(This is defined as time from randomisation to first increase in dexamethasone dose. An increase in dexamethasone dose is defined as **a change from the baseline of  $\geq 8\text{mg/day}$**  for at least 21 days (i.e. the increase is sustained for at least 21 days consecutively). The earliest date when the **dexamethasone dose was  $\geq 8\text{mg/day}$**  compared to baseline or sustained nadir in this period will be used for comparison between the treatment groups. Sustained nadir refers to the highest steroid dose taken during a  $\geq 21$  days period where the patient is consistently taking a lower dose of steroids compared to the baseline dose.)

- Average daily steroid dosage change from baseline until first progression
- Average number of progression/steroid free days

- Time to deterioration of neurological status (assessed via Neurological examination) or death

### 2.6.2 Patient reported outcomes (PROs)

- Neurological symptoms (visual disorder, motor dysfunction, communication deficit, and drowsiness) as measured by the EORTC brain tumour module BN-20.
- Quality of life as measured by the EORTC QLQ-C30 and other domains as measured by BN-20 questionnaire

### 2.6.3 Safety

- Adverse Events (AE)
- Vital signs including blood pressure (BP)
- Electrocardiogram (ECG) parameters
- Laboratory findings (clinical chemistry, haematology, urinalysis, TSH, T3 and T4)
- Physical examination including neurological examination

### 2.6.4 Pharmacodynamic and Pharmacogenetic

- Levels of soluble markers of angiogenesis and tumour growth including changes from baseline using optional blood samples
- Biomarker analysis from archival and postmortem tumour samples (both optional), including:
  - IDH1 and 2 (Yan et al. 2009)
  - MGMT methylation status
  - EGFR, EGFRvIII and PTEN (Mellinghoff et al. 2005)
- Pharmacogenetic analysis using optional blood samples and/or tumour samples

Patients will give separate optional consent for donation and use of archival tumour samples and/or trial blood samples, and/or post-mortem tumour samples.

## 2.7 Trial activation

UCL CTC will ensure that all trial documentation has been reviewed and approved by all relevant bodies and that the following have been obtained prior to activating the trial:

- Research Ethics Committee approval
- Clinical Trial Authorisation from the Medicines and Healthcare products Regulatory Agency (MHRA).
- 'Adoption' into NIHR portfolio
- NHS permission
- Adequate funding for central coordination
- Confirmation of sponsorship
- Adequate insurance provision

---

## 3.0 Selection of Sites/Site Investigators

### 3.1 Site selection

In this protocol trial “**Site**” refers to the hospital or site where trial-related activities are actually conducted.

Sites must be able to comply with:

- Trial treatment(s), imaging, follow up schedules and all requirements of the trial protocol
- Requirements of the Research Governance Framework and the Medicines for Human Use (clinical trials) Act (SI 2004/1031 and all amendments)
- Data collection requirements
- Collection, preparation, temporary storage and shipment of biological samples where agreed

